### Monitoring

#### Data Monitoring

Each clinical site will perform internal quality management of study conduct, data collection, documentation, and completion. All sites will follow a common quality management plan. Before we began data collection, the PIs and the DSMB chair reconfirmed that our sites have appropriate safety measures in place. The DSMB met with the entire research team to review the study protocols. Particular attention was paid to outcome definition, study design, procedures for recording and reporting adverse events (AEs), informed consent procedures, and documentation. At its initial meeting, the DSMB approved the protocol and formulated its operating procedures (eg, meeting schedule, report deadlines for the study statistician, unblinding policy, and guidelines for releasing interim data to the investigators). At this meeting, the plans for interim monitoring for efficacy and futility were presented to the DSMB to aid in trial oversight. We will train competent staff to conduct the assessments and ensure that they understand the data collection procedures and process as well as AE reporting requirements.

#### Effectiveness Study: Monitoring for Harms

Patients who receive care at the practices randomized to implement the 5-Cog paradigm may experience minimal risk through their participation. It is possible that patients may feel shame, anxiety, and some emotional discomfort when completing the cognitive assessment; however, this may be the case with the standard of care cognitive assessment as well and may not be specific to the intervention arm. In addition, in our ADRD screening trial that evaluated the potential benefits and harms of ADRD screening, there were no differences between the screened and control groups in quality of life, depressive symptoms, or anxiety [114,115]. That trial also assessed the impact of this early diagnosis on participants’ quality of life and care and found no negative impact on quality of life, depression, anxiety, health care use, or independence at home [114,115]. The risk of potential harm such as stigma is not known. However, the early detection of ADRD is considered part of the standard of care, and screening for ADRD is part of the AWV covered by Medicare because of the significant potential benefits.

#### Implementation Study: Monitoring for Harms

Answering questions on surveys and participation in interviews with trained personnel involve minimal psychological, social, or other risks. We do not expect any AEs during these noninvasive assessments.

#### Full Study: Monitoring for Harms

Safety oversight will be under the direction of a DSMB composed of individuals with the appropriate expertise. We will set up a data safety monitoring plan, which will be monitored by the PIs and DSMB. The PIs will also conduct data and safety monitoring and will regularly monitor study progress, goal achievement, and overall research direction in consultation with the coinvestigators. Members of the DSMB will be independent from the study conduct and free of conflicts of interest. The DSMB, which will meet at least semiannually to assess safety and efficacy data from each study arm, will operate under the rules of an approved charter that was written and reviewed at its organizational meeting. The DSMB will provide its input to the National Institute of Neurological Disorders and Stroke and NIH staff.

AEs will be monitored on an ongoing basis by the study managers through self-initiated reports from participants or patients, observations of research and clinic staff at the intervention sites, biannual review of acute care use among enrolled patients, and review of EMR data at 90-day outcome collection for any medical records or notes of medical, psychological, or stress symptoms possibly related to the administration of the 5-Cog battery. In addition, a list of hospitalizations and emergency department visits (for any reason) occurring within 90 days after the clinic visit will be generated by the EMR system, which will be reviewed by the PIs and study investigators. All AEs not otherwise precluded per the protocol will be captured on the appropriate case report form. Information to be collected includes event description, time of onset, clinician’s assessment of severity, relationship to study procedures (assessed only by those with the training and authority to make a diagnosis), and time of resolution or stabilization. All AEs occurring during the study will be documented appropriately regardless of their relationship to the intervention and followed until adequately resolved. Any preexisting medical or psychiatric conditions at screening will be considered baseline and not reported as an AE. However, any deterioration in a patient’s clinical or psychological condition during the assessment will be recorded as an AE. Changes in AE severity will be documented to assess the duration of the event at each severity level. For AEs characterized as intermittent, the onset and duration of each episode will be documented. New diagnoses of MCI or dementia may result in psychological stress for patients that may not be captured in the EMR. Hence, we will also assess these more subtle psychological symptoms during the implementation interviews.

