### Trial Design

Given the problems of underdiagnosis and undertreatment of dementia, which are expected to worsen with the growing number of aging adults globally [69], we chose a hybrid type 1 effectiveness-implementation design for this trial. In this design, the primary emphasis is on testing the intervention, with a secondary emphasis on exploring implementation-related factors [55]. We chose this design because it would be premature to conduct an implementation-only trial, given that the 5-Cog has previously been studied in 1200 individuals in only 1 urban primary care setting. The hybrid type 1 effectiveness-implementation design allows us to confirm the effectiveness of our intervention, while also hastening its potential to make needed impact in the “real world” through incorporating implementation examination prospectively [55]. The clinical effectiveness (in this case, meaning the degree of beneficial effect [70]) component of the trial will be completed using a pragmatic, cluster randomized design (randomized at the level of the clinic) with intervention clinics receiving the 5-Cog paradigm and control clinics receiving enhanced usual care (cognitive concern information and cognitive impairment detection education provided but no detection approach or clinical decision support tool implemented).

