#### Interventions in the Control Arm (Enhanced Usual Care)

Patients are screened via telephone using the SCQ, as described in the Recruitment of Clinics and Patients subsection. RAs input results into the EMR. Care providers receive positive SCQ results through noninterruptive alerts. Figure 5 presents images of the alerts at Montefiore-Einstein and at IUH. We are calling this arm “enhanced usual care” because care provider are informed about the presence of a cognitive concern in their patient in this group. In addition, as at the intervention sites, care providers at the enhanced usual care sites receive preparatory education (described in the next subsection). The care providers at the control and intervention sites do not overlap.

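### Non-acute adverse events are looked for differently in the two arms, because the active sources are tied to the intervention sites or to the 5-Cog battery

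*Protocol article*

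**What the plan says.** The section Full Study: Monitoring for Harms lists how adverse events (AEs) come to light:

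- reports that patients make themselves;
- "observations of research and clinic staff at the intervention sites";
- "biannual review of acute care use among enrolled patients";
- a chart review at 90-day outcome collection for "notes of medical, psychological, or stress symptoms possibly related to the administration of the 5-Cog battery";
- a list from the electronic medical record (EMR) of all hospitalizations and emergency visits within 90 days, for any reason.

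The section adds that stress from a new diagnosis may not reach the chart and will also be explored in the implementation interviews. It sets a recording rule: "All AEs occurring during the study will be documented appropriately regardless of their relationship to the intervention". It has the DSMB meet at least twice a year "to assess safety and efficacy data from each study arm".

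The control arm is described under Trial Design as having "no detection approach or clinical decision support tool implemented". Under Interventions in the Control Arm: "Patients are screened via telephone using the SCQ", with the result shown to the care provider in a noninterruptive alert.

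**The concern.** A between-arm safety comparison can be interpreted only if events are sought with the same effort in both arms. Here one source is confined to one arm, and another is conditioned on exposure to a procedure that only one arm receives. Two consequences follow.

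First, for symptoms that do not lead to acute care, the 5-Cog arm would show more events even with no true difference. The article gives a reason to want a control rate: it says of emotional discomfort during testing that "this may be the case with the standard of care cognitive assessment as well and may not be specific to the intervention arm".

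Second, the filter is on administration of the battery. Distress that follows a new diagnosis comes later, from the diagnosis and not from the test. A chart note of it does not match the search wording, although the same section names this harm.

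**Working it through.** The article states no AE rate or safety figure, so there is nothing to reproduce. The check is to classify each source by arm and by filter.

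| Source | Limited to one arm? | Filtered on the battery? | Can yield a non-acute event in a control patient? |
|---|---|---|---|
| Self-initiated reports | No | No | Yes, passively |
| Staff observation | Yes, intervention sites | No | No |
| Biannual acute care review | No | No | No (acute care only) |
| 90-day chart review | Not by site | Yes | Not on a literal reading |
| Hospitalization and emergency visit list | No | No | No (acute care only) |
| Implementation interviews with patients | Yes | Yes, through eligibility | No |

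The interview row rests on three places. Textbox 1 admits patients to the implementation study only if they have had the 5-Cog battery. Recruitment of Clinics and Patients and Interventions for the Implementation Study both place recruitment at intervention sites. The maximum of 132 interviews under Planned Sample Size equals 6 × 22, which would count control practices as well. Even so, the eligibility rule admits no control patient.

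For non-acute events in control patients, the only source left is spontaneous reporting. No active source covers them.

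**Size of the bias, as an illustration.** Assume equal arm sizes, equal true non-acute event rates, and no overlap between sources. Let N be the non-acute events found in the 5-Cog arm, and let s be the share of them that only the one-arm or filtered sources supply. The shared sources then find (1 − s)N in each arm, so the apparent ratio is N / [(1 − s)N] = 1/(1 − s):

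- s = 10%: 1/0.90 = 1.11
- s = 20%: 1/0.80 = 1.25
- s = 50%: 1/0.50 = 2.0

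The document does not give s. For hospitalizations and emergency visits s = 0, and the ratio stays at 1.0.

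**Diagnosis-related stress.** Randomization is 1:1 within site, so each arm has 3 Bronx and 8 Indiana clinics, or 11 × 300 = 3300 patients. The statistical plan expects new diagnoses in 14% and 2%: 3300 × 0.14 = 462 and 3300 × 0.02 = 66. If a proportion d of newly diagnosed patients had charted stress, the literal search would pass over 462d and 66d such notes, a difference of 396d. This error hides a possible excess, so it runs against the first one. The 462 and 66 are expected diagnoses, not harms.

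**Search wording against recording rule.** The rule covers all AEs whatever their cause, and relationship to study procedures is a field completed for each event. The chart review applies a relatedness test before an event is recorded. An unrelated outpatient event is thus recordable but not sought in the chart.

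**The case against.** The strongest reply has four parts.

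- **Shared sources exist.** Three of the five listed sources have no limit by arm or by relatedness, and they include the most serious events. This stands. A reader might infer that the DSMB's by-arm safety data as a whole cannot be compared; the text does not support that.
- **The recording rule is not contradicted outright.** It governs events that have come to light, while the chart wording describes one way of finding them. Capture on the case report form is also qualified by an exception for AEs that the protocol precludes. This largely stands: the two sentences need reconciling but are not incompatible rules.
- **The authors saw the gap on diagnosis-related stress.** They did, and added interviews. But interviews are planned at up to 6 per practice across all types of informant, and no control patient can be interviewed, so they give no control rate.
- **Details belong in the DSMB charter and monitoring plan, which are not shown.** It is true that the article specifies no comparative AE table, so any prediction of what the tables will show is inference. But the article is not silent on detection: it states an asymmetric rule.

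The trial is also described as minimal risk, and the article cites an earlier screening trial that found no difference in depression, anxiety or quality of life. That lowers the stakes but does not make the ascertainment equal.

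**Conclusion.** The point holds for non-acute medical, psychological and stress events. As written, every active way of finding them works only in the 5-Cog arm, and a by-arm reading would be biased toward more events there. Charted distress from a new diagnosis, which can arise in both arms, is outside the literal search. Acute events remain comparable, and the primary analysis is unaffected.

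The size cannot be fixed from the document; the ratios of 1.11 to 2.0 depend wholly on the assumed share s. A reader might go further and attach counts. For example, if 1–3% of patients had a relevant note and half were called possibly related, the review would give about 17–50 events (3300 × 0.01 × 0.5 = 16.5; 3300 × 0.03 × 0.5 = 49.5) against none in control. Those rates are not in the article, and the zero depends on reading one phrase literally. Nor does the text show that the DSMB would be unable to judge risk at all.

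A lesser matter: Masking says that data abstractors are blinded to allocation, yet looking for battery-related symptoms requires knowing who had the battery. This matters only if the same staff do both tasks, which the article does not say.

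This is an inexpensive improvement to the monitoring wording, not a flaw in the trial's main inference.

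**What to change.** 1. Reword the 90-day chart review as an arm-neutral search: one prespecified list of event terms, not conditioned on the battery, applied identically and over the same window in both arms.
2. Judge relationship to study procedures afterwards, in the field already planned. That field is wide enough to cover the telephone questionnaire in the control arm.
3. List intervention-only sources (staff observation and interviews) separately, and restrict the between-arm safety comparison to sources collected the same way in both arms.
4. Reconcile the search wording with the sentence on documenting all AEs regardless of relationship.

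The cost is a change of wording in the monitoring plan and one search run on records already opened at 90 days in both arms for outcome collection. The downside is more unrelated background events in the listings.

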### Auditing

Quality control procedures will be implemented. In the implementation study only, regarding informed consent, study staff will review both the documentation of the consenting process and a percentage of the completed consent documents to evaluate compliance with good clinical practice, accuracy, and completeness. Feedback will be provided to the study team to ensure that proper consenting procedures are followed. To assess data accuracy (the level of correctness of stored information [116]), site staff will compare a representative sample of source data against the database, focusing on key data points. The study team will review protocol deviations on an ongoing basis and implement corrective actions if deviations reach a concerning level. Should independent monitoring become necessary, the PIs will provide direct access to all trial-related sites, source data and documents, and reports for monitoring and auditing by the funding agency and inspection by local and regulatory authorities.

### Ethical Considerations

The Albert Einstein College of Medicine IRB approved this study (2022-14144) and serves as the IRB of record for both sites under a reliance agreement with the Indiana University IRB. This study will be conducted in accordance with federal publication and data-sharing policies and regulations. Regarding consent for participants, we received a waiver of informed consent from individual patients from the IRB to maintain the pragmatic design of the clinical trial. For the implementation part of the study, consent is obtained from all participants before completion of any study measures. Participants who consent for the implementation study receive US $25 in compensation for completed interviews. Outcomes will be extracted and aggregated from the EMR and will be deidentified. After the study is completed, the deidentified, archived data will be transmitted to and stored in a data repository with protections in place for patient confidentiality.

## Results

The grant was funded, and the protocol received IRB approval, in September 2022.

### Effectiveness Study

A validation cohort of 76 older patients (mean age 76.5, SD 7.72 y; n=50, 66% women) from dementia centers at Montefiore Einstein was evaluated with the 5-Cog battery to determine optimal cut scores. This was completed by July 2023. Among these 76 patients evaluated by the multidisciplinary care provider team at these centers (neuropsychology, neurology, and geriatrics), the resulting clinical diagnoses were as follows: 32 (42%) had a diagnosis of dementia, 28 (37%) MCI, 12 (16%) subjective cognitive concerns without objective cognitive impairment, and 2 (3%) had no cognitive diagnosis assigned. The mean scores on the PMIS were 5.8 (SD 2.7), Symbol Match 27.2 (SD 18.2), and sMCR 2.4 (SD 1.7). We correlated performance on the individual 5-Cog battery tests with the Blessed Information-Memory-Concentration Test scores (range 0-32; higher scores indicate worse performance), an omnibus test of general mental status (mean 10.3, SD 6.8). The PMIS (Pearson *r*=−0.76; *P*<.001) and Symbol Match (*r*=−0.69; *P*<.001) showed excellent correlation with Blessed scores. While the sMCR was not correlated with Blessed scores (*r*=0.008; *P*=.95), it was correlated (*r*=−0.34; *P*=.007) with walking speed (mean 72.3, SD 25.3 cm/s) in this sample. The PMIS was correlated (*r*=−0.59; *P*<.001) with the 5-item memory recall subtest on the Blessed Information-Memory-Concentration Test (mean 2.9, SD 1.84; higher scores indicate worse performance). Symbol Match was correlated (*r*=0.88; *P*<.001) with the Symbol Digit Modalities Task score (mean 21.2, SD 14.6; lower scores indicate worse performance).

As we examined the sensitivity and specificity data to choose cut scores, we chose to favor sensitivity to minimize missing individuals with true disease in this sample of patients considered high risk because of their cognitive concerns. The cut scores for a *positive* result on the 5-Cog components were as follows: PMIS ≤6 (range 0-8), Symbol Match ≤25 (range 0-65), and sMCR >5 (range 0-7). There was a high rate of completion of the PMIS (75/76, 99%), Symbol Match (76/76, 100%), and sMCR (74/76, 97%) tests on the 5-Cog battery, indicating high acceptability and feasibility of administration of the 5-Cog battery in populations with cognitive impairments.

The DSMB met in July 2023, approved the protocol and data safety monitoring plan, and authorized study enrollment. By October 2023, all 22 clinics had agreed to participate and been randomized. By November 2023, decision support tool integration into the EMRs had been finalized. As of December 2024, a total of 12 clinics had completed onboarding processes (refer to the Methods section, Care Provider Education and Preparation subsection), and 2369 patients had been enrolled.

### Implementation Study

We have completed 6 implementation interviews and 23 implementation surveys over 12 clinic sites.

### Cost-Effectiveness Study

5-Cog 2.0 investigators have already collected procedure and health care cost estimate data for Montefiore-Einstein for a 5-Cog 1.0 CEA. Preliminary results suggest that the 5-Cog paradigm is a cost-effective option compared to “enhanced usual care” for the early detection of cognitive impairment in primary care ([name], BS, unpublished data, December 2024). Investigators have begun collecting cost estimates for 5-Cog procedures and resulting health care costs in the IUH system, as these were not previously collected.

## Discussion

### Anticipated Findings

The results of this 5-Cog 2.0 RCT will provide additional evidence that the 5-Cog paradigm is effective in improving dementia diagnosis. At the same time, the implementation portion of this study will provide critical information about the context, facilitators, and barriers to using the 5-Cog successfully, while the cost-effectiveness portion of this study will offer a practical analysis of the cost implications of the paradigm. Taken together, these study outcomes will allow informed, tailored, and rapid adaptation and dissemination of the 5-Cog paradigm to diverse primary care environments.

Meeting the ongoing and anticipated growing need for timely dementia diagnosis and care has been a focus of much study. Despite the availability of high-quality tools for dementia detection [22], significant gaps remain in real-world application, and the rates and timeliness of diagnosis remain unacceptably low [28,117,118]. This translates to clinical “blind spots” for care providers and missed opportunities for patients. These gaps are even more pronounced among individuals from historically minoritized racial and ethnic groups [5,119]. The 5-Cog paradigm is poised to effectively bridge these gaps. The 5-Cog itself is designed for widespread applicability, with characteristics that make it appropriate for individuals from various cultural, linguistic, and literacy backgrounds [32,33]. The 5-Cog’s simple, fast format also makes it easily adaptable in resource-limited environments in contrast to some cognitive assessment tools that require specialized training or equipment to administer [120,121]. Although the evidence for decision support systems to improve clinical practice is mixed [50,122], the 5-Cog paradigm does build on prior evidence of the efficacy of decision supports in dementia detection [123,124].

### Strengths and Limitations

This study has several strengths. Its results are anticipated to have improved generalizability compared to prior studies for several reasons: its large sample size; the racially and ethnically diverse patient population being enrolled; and the pragmatic nature (using local CHW staff, colocation in patients’ usual sites of care, and a waiver of written informed consent), which may help reduce the hesitancy of individuals from historically marginalized groups to participate in the trial [125]. While the characteristics and specifications of primary care clinic sites will vary, the urban and rural primary care clinic sites in the 5-Cog study are typical of primary care clinics in the United States, especially those that serve underserved individuals from historically minoritized groups. Prior studies of decision supports in dementia were limited by a small sample size and a lack of active control groups [50,122]. The 5-Cog 2.0 study overcomes these limitations. Another strength of this study is that the BIA will form the basis of a tool that can be used to tailor financial adoption and scalability in different practice settings for national implementation. Finally, this study’s unique hybrid effectiveness-implementation design will rapidly generate actionable data to advance progress in closing dementia care gaps. This study is anticipated to have a few limitations. Although the inclusion criteria are intentionally liberal in this pragmatic trial, the trial may not address dementia care gaps for the subset of patients who lack insight into their cognitive impairments and deny having them and are therefore not eligible for the trial. Implementation analyses will allow an exploration of whether and how the 5-Cog can support PCPs’ clinical approach to this subset of patients who do not recognize their own cognitive decline. A limitation of the CEA is that the time horizon is relatively short, and long-term sustainability will need to be assessed in future studies.

